### Recruitment und randomization

Patients are being seen and diagnosed in specialized dysplasia outpatient clinics of the participating study centers. After they provide us their written informed consent, participants fulfilling all required inclusion and exclusion criteria are given a five-digit pseudonym (patient identifier), with the first two numbers indicating the study center and the latter three numbers indicating a sequential patient number. Patients are randomly assigned by their pseudonym with equal probability to either of the two treatment arms, using a 1:1 ratio. Randomization is carried out using the web-based Randoulette randomization service of the Institute for Medical Informatics, Biometry and Epidemiology, University of Munich, Germany. The platform offers a web-based form in which to enter patient identifier, sex, age and study center, as well as the strata of the patient. Access to the randomization service is provided to the two leading investigators at each study center. Patients are stratified by age (>30 or ≤30 years) and study center.

After the information is entered, the study arm is selected according to a predefined randomization scheme, in this case an unblended, stratified block randomization. To maintain allocation concealment, the exact length of blocks is kept secret by the Randoulette randomization service. The entered information, as well as the randomization results, are stored in the Randoulette database.

### Ethical approval

Approval of trial protocol and informed consent documents have been obtained primarily from the University of Munich Institutional Review Board (project number 275-14), followed by the responsible ethics committees and/or state chambers of physicians of the 12 other study centers (University of Munich Institutional Review Board, ethics committee of the Medical Chamber of Westphalia-Lippe, University of Regensburg Institutional Review Board, ethics committee of the Medical Chamber of Hamburg, ethics committee of the Hannover Medical School, State Medical Chamber of Lower Saxony, institutional review board of Berlin, ethics committee of the Medical Chamber of Schleswig-Holstein, ethics committee of the Heinrich-Heine University of Düsseldorf, institutional review board of Greifswald, University of Aachen Institutional Review Board and institutional review board of the University of Ulm).

All study staff commit themselves to the Declaration of Helsinki (2013 version), as well as to all pertinent national laws and the International Conference on Harmonisation of Technical Requirements for Registration of Pharmaceuticals for Human Use (ICH) harmonized tripartite guidelines for Good Clinical Practice issued in June 1996 (http://www.ich.org/fileadmin/Public_Web_Site/ICH_Products/Guidelines/Efficacy/E6/E6_R1_Guideline.pdf) and the European Medicines Agency’s CPMP/ICH/135/95 guideline (July 2002; http://www.edctp.org/fileadmin/documents/EMEA_ICH-GCP_Guidelines_July_2002.pdf). Important protocol modifications will be reported to all relevant parties. All participants complete informed consent forms prior to participation in the trial.

### Inclusion and exclusion criteria

#### Inclusion criteria

Patients with an internal or external diagnosis of histologically confirmed CIN 3, a colposcopically visible lesion and a positive high-risk HPV test (according to the criteria of Meijer *et al*. [21]) who have had no previous cervical surgery, no previous treatment of the disease, are at least 18 years of age and provide written informed consent are eligible for inclusion in the study.

#### Exclusion criteria

Patients are excluded at any time upon their request or if any of the following applies: pregnancy at time of inclusion and during the first 6 postoperative months, intake of immunosuppressants, known HIV infection, malignant disease requiring treatment or inadequate colposcopy.

### Study blinding

To exclude bias by unconsciously different behavior, the study is patient-blinded for the first 6 postoperative months. In case of complications, however, access to the surgical report is possible at any time.

### Surgery

Both surgical techniques are performed using a thin, low-voltage, electrified wire loop known as a *loop electrosurgical excision procedure electrode*. Procedures are performed by experienced surgeons at 13 German dysplasia centers under colposcopic control and are carried out as shown in Figs. 1, 2, 3 and 4. A dysplastic cervical lesion is identified after application of acetic acid and iodine solution.

**Fig. 1 Fig1:**
[figure not shown]
Resection margins of classical large loop excision of the transformation zone operation including the transformation zone, which is defined as 3 to 4 mm around the squamocolumnar junction. CIN, Cervical intraepithelial neoplasia; LLETZ, Large loop excision of the transformation zone; SCJ, Squamocolumnar junction

**Fig. 2 Fig2:**
[figure not shown]
Resection margins in lesion-only operation, where a distance of 2 mm around the lesion should be kept. CIN, Cervical intraepithelial neoplasia

**Fig. 3 Fig3:**
[figure not shown]
Comparison of the extent of both surgical methods, example 1. LLETZ, Large loop excision of the transformation zone; SCJ, Squamocolumnar junction

**Fig. 4 Fig4:**
[figure not shown]
Comparison of the extent of both surgical methods, example 2. LLETZ, Large loop excision of the transformation zone; SCJ, Squamocolumnar junction

In the lesion-only resection, the dysplastic area is removed with a safety margin of 2 mm. In the classical LLETZ, the lesion, including the transformation zone, is resected. Because the outer border of the transformation zone cannot be determined colposcopically, the following definition for resection of the transformation zone was stated after expert consensus. After identification of the squamocolumnar junction, an area of 4 mm surrounding the junction is defined as the transformation zone. In the event that the iodine-negative zone is greater than the defined area, the iodine-negative area is considered the transformation zone and should be removed as well.

Postoperatively, cone size is measured before fixation by submergence in a fluid-filled cylindrical vial using Archimedes’ principle. Afterward the specimen is evaluated histologically for the grade of dysplasia and achievement of resection margins.

### Postoperative controls

According to German guidelines, the first follow-up examination is performed after an interval of 6 months. A Pap smear, HPV test and colposcopy are performed. In cases of colposcopically suspect lesions, a biopsy is taken. A second postoperative control is carried out 12 months after conization.

### Primary outcome measure

The primary endpoint is the rate of negative high-risk HPV tests after 6 months, because a negative HPV test is generally regarded as evidence of successful treatment. The negative predictive value for a negative HPV test after conization is between 92 % [16] and 100 % [22–26], and successful treatment usually leads to the elimination of the virus [27–30]. A negative HPV test therefore excludes CIN persistence or recurrence with high probability. In contrast, repeated positive HPV tests can be taken as suspicious of a continuation of dysplasia or as an indicator of recurrent dysplasia.

### Secondary outcome measure

Because it is possible, from a clinical point of view, that patients who have received the lesion-only operation simply need more time for the viral infection to be eliminated, HPV is tested again in the postoperative control after 12 months. Further secondary endpoints are Pap smear results in both postoperative controls, biopsy results (if applicable) and resection margins.

### Safety concerns

It should be noted that, even with classical conization, resection margins are positive or only questionably negative in up to 25 % of cases.

If there is CIN 1 detectable at the cutting margins, recurrence or persistence is expected in only 0 % to 5 % of participants. In the case of CIN 3 at the surgical margins, recurrence can be expected in 20 % to 25 %. If non in sano resection happens at the endocervical margin, risk increases to 30 %. If both, endo- and ectocervical resection margins are affected with CIN 3, risk is highest with 50 % [31]. Importantly, in those cases where immediate reconization is indicated because of positive surgical margins, no dysplasia was detected in over 80 % of cases.

For this reason, an immediate reconization usually is not indicated, but should be assessed according to individual risk and discussed with the patient. Only after further histological confirmation of CIN during the first postoperative control after 6 months will reconization be recommended.

Thus, the initially conservative approach in terms of a checkup after 6 months is also justified in the case of an increased incidence of positive surgical margins. This can be seen especially in light of the expected reduction of complications associated with surgery.

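### The 12-month HPV comparison cannot separate slow viral clearance from repeat surgery, because women re-excised after the 6-month control and then negative count as negative

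*Protocol article*

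**What the plan says.** The protocol article defines the primary endpoint under Primary outcome measure: "The primary endpoint is the rate of negative high-risk HPV tests after 6 months". Under Secondary outcome measure it adds the 12-month test and its reason: women after the smaller operation may "simply need more time for the viral infection to be eliminated, HPV is tested again in the postoperative control after 12 months". The remaining secondary endpoints follow: "Further secondary endpoints are Pap smear results in both postoperative controls, biopsy results (if applicable) and resection margins". Re-excision is part of neither HPV definition and is not listed as an endpoint.

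Postoperative controls describes the 6-month visit: "A Pap smear, HPV test and colposcopy are performed. In cases of colposcopically suspect lesions, a biopsy is taken".

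Safety concerns has two sentences on repeat surgery. The first says that "an immediate reconization usually is not indicated, but should be assessed according to individual risk and discussed with the patient". The second says: "Only after further histological confirmation of CIN during the first postoperative control after 6 months will reconization be recommended".

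**The concern.** The 12-month test is there to answer one question: does a lesion-only patient who is still positive at 6 months clear the virus if given longer? The women for whom this matters most include those with CIN confirmed at 6 months, and they are the women for whom the article recommends a second excision. If that advice is followed before the next control, their 12-month result describes the outcome of two operations. Under the stated definition a negative result still counts as negative in the randomised arm.

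If the smaller operation leaves more disease, more women in that arm are re-treated, and the arms move together for a reason unrelated to slow clearance. The Abstract says the HPV tests at 6 and 12 months together serve to evaluate equal oncological outcome. A false catch-up at 12 months could therefore soften an unfavourable 6-month result.

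**Working it through.** **1. The plan's own figure.** Inputs from Sample size and statistics: 90 % HPV-negative in both groups, margin 5 points, one-sided α = 0.05, power 80 %.

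n per arm = (z₀.₉₅ + z₀.₈₀)² × (0.90×0.10 + 0.90×0.10) / 0.05² = (1.645 + 0.842)² × 0.18 / 0.0025 ≈ 445.1, rounded up to 446. The total is 892, as stated. With 10 % dropout, 892/0.90 gives 992, which the article rounds to 1000. No stated figure is wrong on this point.

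**2. Order of events.**

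| Re-excision | When | Can alter the 6-month HPV result? | Can alter the 12-month HPV result? |
|---|---|---|---|
| Immediate, decided individually | Before the 6-month control | Yes | Yes |
| Recommended after CIN is confirmed | After the 6-month control, where the primary HPV sample is taken | No | Yes, if done before the 12-month control |

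**3. Size at 12 months.** Hidden excess = (difference between arms in reconization rate) × P(would still be HPV-positive at 12 months) × P(negative after reconization). The article gives none of the three. Assume the second is 1 and the third is 0.8 to 0.9. Each percentage point of difference in reconization then hides 1 × 1 × 0.8 to 0.9 = 0.8 to 0.9 points of HPV excess. This is an upper range: re-excision is triggered by histology, and some of these women would have become HPV-negative without it.

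**4. Size at 6 months.** Inputs:
- Control margins positive or questionable: 25 % (Safety concerns, stated as an upper value).
- Lesion-only margins positive: 35 % (assumption; the article gives no figure).
- Share of margin-positive women re-excised early: 5 % to 20 % (assumption).
- Share of those who would otherwise fail: 20 % to 25 %. This is the recurrence risk for CIN 3 at the margins in Safety concerns, used as a stand-in for HPV positivity. All are assumed to turn negative.
- Failure rates without early re-excision: 10 % and 15 %, exactly at the margin (illustration).

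Masked difference = (0.35 − 0.25) × share re-excised × share otherwise failing.
- Low: 0.10 × 0.05 × 0.20 = 0.001, or 0.1 points.
- High: 0.10 × 0.20 × 0.25 = 0.005, or 0.5 points.

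P(non-inferiority declared) = Φ[(0.05 − d)/SE − 1.645], where d is the observed difference, SE = √[(p_C(1−p_C) + p_E(1−p_E))/446], and p_C and p_E are the observed failure rates.
- No masking: d = 0.05, giving 5.0 %.
- Low: p_C = 0.10 − 0.0025 = 0.0975; p_E = 0.15 − 0.0035 = 0.1465; d = 0.049; SE = 0.0219; result 5.5 %.
- High: p_C = 0.10 − 0.0125 = 0.0875; p_E = 0.15 − 0.0175 = 0.1325; d = 0.045; SE = 0.0209; result 8.0 %.
- Equal margin positivity and equal early re-excision: d stays 0.05, result 5.0 %.

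**5. Would counting early re-excision as failure suit the primary endpoint?** With 20 % re-excised early, 0.35 × 0.20 = 7 % of lesion-only and 0.25 × 0.20 = 5 % of control women are re-excised, a difference of 2.0 points. Only 0.4 to 0.5 points of that are true failures. If all re-excised women test negative, the rule recovers 0.4 to 0.5 points and adds 1.5 to 1.6 points from women who would not have failed.

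**The case against.** The strongest reply is that this is an article, and that the handling of re-treated women may stand in the full protocol or analysis plan. No sentence says such women count as successes; that follows only from the definition. This stands as a caution. The point here, however, is a clash between two things the article does state: the purpose of the 12-month test, and a management rule that changes the result in the women the test is about.

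A second reply is that failures are not invisible. The 6-month HPV result is recorded before any reconization recommended at that visit, and biopsy, Pap smear and margin results are separate endpoints. That is true, and it protects the formal non-inferiority test. It does not make the 12-month HPV comparison interpretable.

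A reader might infer that the 6-month non-inferiority test is itself biased. The documents do not support this:
- Recommended reconizations follow the primary sample, and immediate reconization is described as usually not indicated.
- A rise in positive margins is mentioned only as a possibility, and unequal early re-excision is nowhere stated.
- A false non-inferiority rate near 13 % (12.8 %) arises at 35 % versus 25 % margins and 20 % early re-excision if half of those women would otherwise be HPV-positive. Applied to all margin-positive women, that share gives 0.25 × 0.50 = 12.5 % HPV-positive in the control arm from this group alone, against a planned total of 10 %. In the article, 50 % is the recurrence risk only when both margins carry CIN 3.
- At the 20 % to 25 % risk and the same 20 % early re-excision, 12 % to 15 % would need half of lesion-only margins to be positive, a figure the article does not give.
- The article also reports that over 80 % of immediate reconizations found no dysplasia.

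A reader might also see a flat contradiction between the two reconization sentences. They can be read as a general rule with an individual exception.

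**Conclusion.** The concern holds for the 12-month secondary comparison. As defined, it cannot show whether lesion-only patients only need more time, because repeat surgery and slow clearance give the same negative result. The direction is towards apparent equality if lesion-only surgery fails more often, which is not known. The size cannot be derived from the documents; 0.8 to 0.9 points per point of excess reconization is an upper range. It also rests on reconization being done before the 12-month control.

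For the 6-month primary endpoint only individually decided immediate reconizations matter. The bias is nil if they are equally frequent in both arms. It is about 0.1 to 0.5 points, with false non-inferiority of about 5.5 % to 8 % instead of 5 %, under the inputs in step 4 of the working. All of those are assumptions except the 25 % control margin rate and the 20 % to 25 % risk. This does not justify changing the primary endpoint.

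**What to change.** **12 months.** Define success as a negative high-risk HPV test and no repeat excision or other cervical treatment since the study operation. Count re-treated women as failures in their randomised arm. Report the plain HPV result alongside, and report reconization by arm with its timing.

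**6 months.** Keep the HPV result as the primary endpoint. Add a sensitivity analysis that counts women re-excised before the 6-month test as failures. It should stay a sensitivity analysis, because it ties the outcome to individual decisions by surgeons who know which operation was done, and because it can over-correct, as step 5 of the working shows.

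**Wording.** The investigators should make the two sentences on immediate and later reconization consistent. Which applies is for the clinicians.

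**Cost.** Reconization dates must be recorded, and the 12-month success rate falls slightly. The primary endpoint is unchanged, so the calculation of 892 stands.

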### Interim analysis and stopping rules

An interim analysis will be performed at the postoperative 6-month control of the first 250 patients included. The primary outcome is the result of HPV tests. If the rate of positive HPV tests after 6 months in patients who have undergone lesion-only surgery is higher by more than 15 % than among patients who have had classical LLETZ, the study will be terminated. Because the interim analysis was included exclusively for safety reasons and thus does not involve a test of the non-inferiority study hypothesis, the probability of a type I error (that is, a false-positive study result) should not be affected.

### Additional investigations

Because HPV infection is the cause of dysplasia, further analyses to investigate HPV infection are performed in a subset of 250 patients. A particular focus is on the genotyping of HPV infection because often multiple infections with different HPV types are present simultaneously, especially in young patients. Thus, there is the risk that, despite eradication of the lesion-causing HPV type, the conventional HPV test result may continue to be positive because infection with another HPV type is present without clinical consequence.

To make a statement with respect to a more valid clinical consequence of HPV infection, detection of transcriptional activity of E6 and E7 is analyzed. Expression of viral oncoproteins E6 and E7 plays a crucial role in HPV-mediated carcinogenesis, as it interferes with the cell cycle, causes cell cycle progression (E7) and at the same time prevents apoptosis (E6). This occurs through the inactivation of oncosuppressor proteins p53 and retinoblastoma protein (pRb). pRb in particular prevents cells from entering S-phase and thus has antiproliferative effects [32–37]. As opposed to the mere detection of HPV DNA, testing for the transcriptional activity of E6 and E7 can allow us to make a statement about the biological activity of the infection.

The described additional analyses are performed at five study centers (Munich, Hannover, Wolfsburg, Berlin and Regensburg).

## Discussion

With knowledge about the obstetric complications of cervical conization, surgical radicalism has increasingly declined in recent years. To date, it has not yet been systematically analyzed whether consistent oncological safety can be guaranteed by removing less tissue. In discussions about the optimal extent of conization with leading colposcopists in Germany, it furthermore turns out that the size of the cone varies significantly, depending on the individual surgeon.

The aim of this study is thus to define a universal standard for cervical conization that combines the highest level of oncological safety with minimal obstetric risk. To that end, we compare two surgical methods with each other: (1) classical LLETZ, in which the lesion is removed, including the transformation zone; and (2) excision of the lesion only.

There are certain limitations to our study. In patients in whom the entire transformation zone is affected by the lesion but who will be randomized into the lesion-only group, the extent of the operation would in fact be the same as in patients randomized to undergo the classical LLETZ operation. This could ultimately lead to limited discrimination between the two study groups. To evaluate this influence on the results, every surgeon must indicate the extent of the dysplastic area (CIN/ectocervix in percent) at the time of the operation. However, including only patients with small lesions would lead to a severe selection bias by recruiting patients according to more subjective criteria. Furthermore, generalization of the study results could no longer be guaranteed, because only a subgroup of patients with high-grade dysplastic lesions would be included.

## Trial status

As of May 2015, we are still recruiting participants.

## Abbreviations

CIN: Cervical intraepithelial neoplasia
ECO-ROCS: Evaluation of Clinical Outcome after Reduction of Conization Size trial
HPV: Human papillomavirus
ICH: International Conference on Harmonisation of Technical Requirements for Registration of Pharmaceuticals for Human Use
LEEP: Loop electrosurgical excision procedure
LLETZ: Large loop excision of the transformation zone
pRb: Retinoblastoma protein
SCJ: Squamocolumnar junction
